**Figure 3 fig3:**
[figure not shown]
EA treatment points. 犊鼻: Du Bi (ST35), 内膝眼: Nei Xi-Yan (EX), 曲泉: Qu Quan (LR8), 膝阳关: Xi Yang-Guan (GB33), 伏兔: Fu Tu (ST32), 梁丘: Liang Qiu (ST34), 足三里: Zu San-Li (ST36), 丰隆: Feng Long (ST40), 鹤顶: He Ding (EX), 血海: Xue Hai (SP10), 阴谷: Yin Gu (KI10), 阴陵泉: Yin Ling-Quan (SP9), 三阴交: San Yin-Jiao (SP6), 太溪: Tai Xi (KI3), 风市: Feng Shi (GB31), 阳陵泉: Yang Ling-Quan (GB34), 外丘: Wai Qiu (GB36), 悬钟: Xuan Zhong (GB39), 足临泣: Zu Lin-Qi (GB41), 委阳: Wei Yang (BL39), 委中: Wei Zhong (BL40), 承山: Cheng Shan (BL57), 昆仑: Kun Lun (BL60).

### Fu’s subcutaneous needling group

5.2

The disposable FSN produced by Nanjing Paifu Medical Technology Co. (Figure 1), and the specific operation will be as follows:(1) Body position: the subject will be asked to lie supine with knees straight and pelvis in neutral position.(2) Choose the needle entry points (Figure 4): Including 1 necessary point, which is a reference to previous studies (15, 20), the quadriceps muscle is selected and the entry point is between the line connecting the anterior superior iliac spine and the upper 1/3 of the lateral superior border of the patella. According to different pain sites, clinical manifestations and the finding of the affected muscle, choose 1 to 3 optional points among the following points of needle entry: A for pain in the posterior side of the knee, choose the midpoint of the line connecting the popliteal fossa and the heel. For lateral knee pain, choose B the lateral border of the tibia, at the midpoint of the line between the external knee eye and the tip of the external ankle, or C the upper 1/3 of the line between the highest point of the greater trochanter of the femur and the upper outer edge of the patella. For medial knee pain, choose D the lower 1/4 of the line connecting the midpoint of the pubic symphysis with the inner superior border of the patella, or E the upper 1/3 of the line connecting the tip of the inner medial ankle of the lower leg with the medial tibial condyle.(3) Needle insertion: After selecting the needle insertion point, the therapist carries out routine disinfection, and then selects a disposable medium-gauge FSN (produced by Nanjing Paifu Medical Science and Technology Co., Ltd.), which is placed in the FSN insertion device (produced by Nanjing Paifu Medical Science and Technology Co., Ltd.), with the tip of the needle exposed outside of the flexible cannula, and the tip of the needle inserted in the direction of the knee joint, rapidly entering the subcutaneous layer of loose connective tissue around the affected muscle until the needle is completely immersed in the subcutaneous tissue. To confirm that the needle does not extend into the dermis or muscle, the participant must confirm that there is no pain at all during the entire insertion process.(4) Swaying movement: The handle of the needle is held in the hand and the needle is swung from side to side in a fan shape. The fan angle is approximately 60°, and the swaying movement time for each needle entry point is 2 min, 200 times. Throughout the swaying movement, participants must confirm that they feel no pain at all.(5) Reperfusion Approach (RA): the subject was required to do 3 cycles of RA for each movement, each cycle included 10 s of continuous movement and 10 s of rest, totaling 1 min, the specific RA is shown in Figure 5.1 RA of mandatory points: the patient was placed in supine position, and the subject was asked to dispose of the popliteal fossa of the affected leg at the edge of the bed, with the calf suspended perpendicular to the treatment bed, and the therapist applied a resistance at the patient’s ankle, and the patient was instructed to straighten the knee joint.2 RA at point A: the patient is positioned prone, the treatment staff applies a resistance at the patient’s ankle, and the subject is asked to flex the knee.3 RA at point B: With the patient in the supine position, the therapist applies a resistance at the dorsum of the patient’s foot and asks the subject to perform dorsiflexion of the foot.4 RA at point C: The patient is placed in the supine position and the therapist applies a resistance at the patient’s ankle and asks the subject to perform knee extension.5 RA at point D: The patient is placed in the supine position and the therapist applies a resistance at the patient’s ankles and asks the subject to perform knee extensions.6 RA at point E: With the patient in the prone position, the patient is instructed to perform a knee flexion maneuver and the therapist applies a resistance at the plantar aspect of the patient’s foot and asks the subject to perform a plantarflexion maneuver.

**Figure 4 fig4:**
[figure not shown]
FSN treatment points. According to the soft ruler as a size reference, × represents the position of the needle entry point of the FSN. **(A)** For pain in the posterior side of the knee, choose the midpoint of the line connecting the popliteal fossa and the heel. For lateral knee pain, choose **(B)** the lateral border of the tibia, at the midpoint of the line between the external knee eye and the tip of the external ankle, or **(C)** the upper 1/3 of the line between the highest point of the greater trochanter of the femur and the upper outer edge of the patella. For medial knee pain, choose **(D)** the lower 1/4 of the line connecting the midpoint of the pubic symphysis with the inner superior border of the patella, or **(E)** the upper 1/3 of the line connecting the tip of the inner medial ankle of the lower leg with the medial tibial condyle.

**Figure 5 fig5:**
[figure not shown]
**(A–E)** Patient force and physician’s resistance in the reperfusion approach.

The therapist performs the reperfusion activity with the corresponding movements according to the position of the performed points.(6) Withdrawal of needles: At the end of the treatment, remove the FSN.

## Outcomes measurements

6

Evaluators will be tested for outcomes at baseline, week 1, week 2, week 3, week 4 of treatment, and during follow-up (Table 2).

**Table 2 tab2:** Study schedule.

Time point	Study period						
	Screening	Baseline	Treatment				Follow- up
	(−T1)	(T0)	(T1)	(T2)	(T3)	(T4)	(T8)
Basic information collection							
Eligibility screen	×						
Informed consent	×						
Allocation		×					
Demographic data		×					
Medical and treatment history		×					
Knee joint X-ray		×					
Safety observation							
Adverse event			×	×	×	×	
Therapeutic observation							
Level walking (NRS)		×	×	×	×	×	×
Stair activity (NRS)		×	×	×	×	×	×
6-min walk test		×	×	×	×	×	×
WOMAC		×	×	×	×	×	×
SF-12		×				×	×

−T1, the day before enrolment. T0, the day of enrolment and allocation. T1–T4, the treatment period for 4 weeks. T8, the Fourth week after the end of treatment. NRS, Numerical Rating Scale; WOMAC, the Western Ontario and Mc Master University Osteoarthritis Index; SF-12, Quality of Life Evaluation Scale.

### Primary outcome

6.1

Response rate for knee symptom relief after 4 weeks of treatment (proportion of patients with ≥2-point decrease in joint pain NRS and ≥6-point decrease in WOMAC at the end of 4 weeks of treatment compared with baseline).

### Secondary outcomes

6.2

Response rates for knee symptom relief, knee pain NRS scores, WOMAC scale scores, 6-min walk test, and Brief Quality of Life Scale (SF-12) scores at 1, 2, and 3 weeks of intervention and 4 weeks after the end of intervention.

### Safety evaluation

6.3

Adverse events related to FSN and needling occurred during the study period, including subcutaneous hemorrhage, needle fainting, needle breakage, etc., will be recorded, as well as the entry point of FSN selected for each treatment and the acupoints selected for electroacupuncture.

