**Methods and analysis:**

This study is a prospective, multicenter, randomized controlled trial to compare the efficacy and safety of FSN with EA in the treatment of KOA. This study intends to recruit 300 patients with osteoarthritis of the knee in 6 tertiary hospitals in China, including Shandong Provincial Third Hospital, Shandong University, etc. The group was randomly divided into FSN group and EA group according to 1: 1 ratio. The intervention time is 30 min, and the treatment was carried out three times a week for 4 weeks, and the long-term follow-up was carried out one month after the treatment. The primary outcome index was the response rate of knee symptom relief, and the secondary outcome indexes were the numerical assessment of knee pain (NRS), WOMAC osteoarthritis index, quality of life evaluation (SF-12), 6-min walk test and safety evaluation.

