## Highlights

Firstly, this is a multicenter, large-sample study. It will provide strong evidence for the efficacy and safety of FSN in the treatment of KOA.Secondly, we will conduct this trial in strict compliance with the protocol in order to realistically evaluate the efficacy.Thirdly, blinding is not possible for both operators and participants.Fourthly, patients recruited from various centers may differ in gender, age, and other disorders, so subgroup analyses may be necessary to determine the effectiveness of FSN in different subgroups.Fifthly, this study did not have a sham-Fu’s subcutaneous needling group to remove the placebo effect.

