### The design of study

2.1

In this study, 300 patients with KOA will be recruited in six tertiary hospitals in China, including Shandong Provincial Third Hospital, Shandong University, from January 2024 to June 2026, and randomly divided into the FSN group and the EA group, with 150 cases in each group, to validate the clinical efficacy of the multicenter and large sample.

Subjects will receive either FSN or EA treatment. Both groups will be treated for 4 weeks, with 3 treatments per week and 1 treatment every other day, for a total of 12 times. The primary outcome measure is the response rate of knee symptom relief after 4 weeks of treatment (the proportion of patients with a decrease of ≥2 points on the NRS and a decrease of ≥6 points on the WOMAC at the end of 4 weeks of treatment compared with baseline). Secondary outcome indicators is the response rate of knee symptom relief, NRS, WOMAC scale score, 6-min walk test at 1, 2, 3, and 4 weeks of intervention and 4, 12, and 24 weeks after the end of intervention, as well as the Brief Quality of Life Scale (SF-12) score at 1, 4, and 4 weeks after the end of intervention. The flow chart of this experiment is shown in Figure 1.

The study and experimental procedures were approved by the Institutional Review Board. All subjects will be recruited from 6 centers in the country (Figure 2).

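### Section 6.3 makes relatedness a condition for recording an adverse event, at odds with Table 2 and the CRF description, and Table 2 schedules no adverse-event collection at T8

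*Protocol article*

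**What the plan says.** The recording rule is in Section 6.3 (Safety evaluation). What is to be recorded is "Adverse events related to FSN and needling occurred during the study period", with bleeding under the skin, fainting and needle breakage given as examples. The same sentence adds that the FSN entry points and the electroacupuncture points chosen at each treatment are noted.

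The schedule is in Table 2 (Section 6, Outcomes measurements). One header, for the study period, spans every column from screening to follow-up. Under safety observation there is a single row, "Adverse event", marked at T1, T2, T3 and T4 and empty at T8. The footnote defines the last column: "T8, the Fourth week after the end of treatment".

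Section 8 (Ethics and dissemination) lists what each CRF must contain. Adverse events are on the list without any condition on cause, next to the treatment assignment.

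Safety is part of the trial's purpose. The Abstract gives the comparison of efficacy and safety between the two treatments as the aim, and the Highlights state: "It will provide strong evidence for the efficacy and safety of FSN in the treatment of KOA".

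On blinding, the Highlights say that "blinding is not possible for both operators and participants". Section 4 (Randomization and blinding) adds that the staff who collect and analyse the data are kept unaware of allocation.

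The length of follow-up is stated in two ways. The Abstract says "the long-term follow-up was carried out one month after the treatment", which agrees with Table 2. Section 2.1 (The design of study) gives visits at "4, 12, and 24 weeks after the end of intervention".

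**The concern.** There are two separate problems.

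The first is what gets recorded. Under Section 6.3 an event qualifies because it is related to the needling, so a causality judgement comes before data entry. An event judged unrelated has no stated route into the record and cannot be looked at again later. In a comparative safety assessment, an all-cause count by arm is the safeguard against attribution that differs between arms. If only related events are kept, that safeguard is gone, and no analysis plan can restore it because the data do not exist.

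The second is when events are collected. The rule in Section 6.3 covers the study period, but the schedule that site staff would follow stops at the end of treatment. Events that begin or are noticed after the last treatment visit have no scheduled point of collection, although patients are seen at T8 for every efficacy measure.

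What is at stake is the safety comparison that the article sets out to deliver, not the efficacy result.

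**Working it through.** The article gives no adverse-event rate and no safety calculation, so there is no safety figure to reproduce. The check sets the passages side by side and then counts weeks.

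**1. Which events are recorded**

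- Section 6.3: events related to the needling.
- Table 2: adverse events, with no condition on cause.
- Section 8, CRF contents: adverse events, with no condition on cause.

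The rule written out in full is the narrow one, and the two shorter mentions are unqualified. A site cannot tell from these passages whether an event thought to be unrelated should be entered.

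**2. Who judges relatedness**

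- Operators and participants know the treatment (Highlights, Section 4).
- Data collectors and analysts are said not to know it (Section 4).
- No passage names the person who decides whether an event is related.
- Deciding that an event was caused by FSN or by electroacupuncture largely requires knowing which was given. Section 6.3 records the needle sites in the same sentence as the events, and the CRF in Section 8 holds the assignment and the events together.

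So the judgement is not assigned to a blinded assessor and cannot readily be blinded. The documents do not show who makes it.

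**3. When events are collected**

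- Section 6.3: throughout the study period.
- Table 2: T8 lies under the study-period header. The adverse-event row is empty there, while both NRS rows, the 6-min walk test, WOMAC and SF-12 are all marked at T8.

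The row has a cell for every column, and the efficacy rows below it are filled at T8, so the gap does not look like a truncated table.

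**4. Size of the gap in calendar time**

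Inputs: 4 weeks of treatment with scheduled collection (Table 2), and follow-up of 4 weeks (Table 2, Abstract) or up to 12 or 24 weeks (Section 2.1).

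Formula: share without scheduled collection = follow-up weeks / (4 + follow-up weeks).

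- Follow-up of 4 weeks: 4 / (4 + 4) = 4/8 = 50%.
- Follow-up of 12 weeks: 12 / (4 + 12) = 12/16 = 75%.
- Follow-up of 24 weeks: 24 / (4 + 24) = 24/28 = 86%.

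These are shares of time under observation, not shares of expected events.

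**The case against.** The best defence has four parts.

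*Section 6.3 does not say that other events are discarded.* This is correct, and Table 2 and Section 8 are unqualified. A reader might infer that the trial records only related events; taken together the passages do not establish that. What stands is that they disagree, and that the one sentence stating the rule is the restrictive one.

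*The data collectors are blinded.* Section 4 says so. A reader might infer that the safety comparison depends on unblinded attribution, but that goes beyond the text, because no assessor of relatedness is named. A condensed article may also leave the assessor's identity to the full protocol. The missing name is therefore not the defect. The defect is a rule that puts the judgement before recording, where blinding would be hard to achieve.

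*The uncovered weeks contain no needling.* All 12 sessions fall in weeks 1 to 4, and the examples in Section 6.3 (bleeding under the skin, fainting, needle breakage) occur at or near a session. This stands as a limit on the size: 50% of the time is probably well under 50% of the procedure-related events. It does not remove the contradiction between the rule and the schedule.

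*An empty cell does not forbid recording.* A patient could report an event at T8 unprompted, and a lasting pain flare would show on the NRS and WOMAC. That is fair, but nothing in the schedule asks for such events, and spontaneous reporting is not a basis for comparing two arms.

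**Conclusion.** The point holds as two inconsistencies with consequences for the data. Section 6.3 ties recording to relatedness, which is narrower than Table 2 and the CRF description and puts a judgement that is hard to blind ahead of data entry. Table 2 also leaves T8 without adverse-event collection, against the study-period wording of Section 6.3.

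The gap is 4 of 8 weeks (50%) on the follow-up in Table 2 and the Abstract, rising to 24 of 28 weeks (86%) if the longest visit in Section 2.1 applies. Which of these is correct cannot be settled from the article, because its follow-up statements conflict.

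No size can be put on any bias between the arms. A reader might try to work out a spurious difference in event rates, but the article gives neither an event rate nor any sign that attribution differs by arm, so the result would only reflect the values assumed.

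This should be corrected, because comparative safety is a stated objective and unrecorded events cannot be recovered reliably. It does not affect the primary outcome or the sample size.

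**What to change.** - Reword Section 6.3 so that all adverse events in both arms are recorded from first treatment to the last follow-up visit, whatever their cause, with relatedness held as a separate field.
- Mark the adverse-event row at T8 in Table 2. Reconcile the follow-up in Section 2.1 with Table 2 and the Abstract, and if later visits are kept, mark the row there as well.
- Compare all-cause as well as related events by arm. The format of that comparison can be left to the statistical analysis plan.

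The cost is one question at a visit that already takes place and slightly more data entry. Treatment, sample size and the T8 visit itself do not change. The change has to be made prospectively: events missed in patients who have already passed T8 could be sought only by recall.

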### Patient and public involvement statement

6.4

Patients and the public will not be involved.

## Statistical analysis

7

Statistical analysis was performed by SPSS26.0 software, and all test data were expressed as mean and standard deviation.

A total of two types of independent variables were used in this study, namely the group independent variable (FSN group and EA group) and the time independent variable (pre-intervention, after 1, 2, 3, and 4 weeks of intervention, and after follow-up), in which the time independent variable was a replicated independent variable. Data were tested for normality using the Shapiro–Wilk test and Leven’s test for chi-square. If the data conformed to normal distribution, two-way repeated measures ANOVA (Two-Way Repeated ANOVA) was used to observe the Main Effect and Interaction of the two types of independent variables, i.e., time independent variable (within-group) and subgroup independent variable (between-groups), on the dependent variable, and when there was an Interaction between the two, a Boneferroni’s *post hoc* test (*Post Hoc*) was used. η^2^ was used for the expression of the effect size: η^2^ < 0.06 is a small effect size. 0.06 ≤ η^2^ < 0.14 is a medium effect size. η^2^ ≥ 0.14 is a large effect size. If the distribution did not conform to normal distribution, the Scheirer-Ray-Hare test was used and results were expressed as median and interquartile spacing.

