### Sample size calculation

3.5

This study is a randomized controlled trial design, the experimental group is the Fu’s subcutaneous needling group, the control group is the acupuncture group, the response rate of the research subjects is the main evaluation index of observation, according to the review of the literature/pre-experimental results, the response rate of the experimental group p1 is 0.56, and the response rate of the control group p2 is 0.45, set the bilaterally *α* = 0.05 that is, unilateral 0.025, the degree of certainty that is, the 1 - *β* is 0.9, and the sample size ratio of the experimental group to the control group is 1:1, the noninferiority threshold is-0.1. The ratio of the sample size of the test group to that of the control group is 1:1, and the non-inferiority cut-off value is-0.1. Referring to the method of Chow et al. (18), the sample size of the test group is 118 cases and the sample size of the control group is 118 cases by using the R language calculation. Considering 20% of lost visits as well as refusal of visits, at least 146 cases in the experimental group and 146 cases in the control group were eventually needed, totaling a sample size of 300 cases for inclusion.

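### The primary endpoint is a yes/no response rate judged against a margin of −10 percentage points, but the stated analysis handles only means or ranks of scores and cannot yield that comparison

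*Protocol article*

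**What the plan says.** Section 6.1 defines the primary outcome as "Response rate for knee symptom relief after 4 weeks of treatment", that is, the "proportion of patients with ≥2-point decrease in joint pain NRS and ≥6-point decrease in WOMAC at the end of 4 weeks of treatment", each decrease being measured from the baseline value. Section 2.1 and the Discussion define it in the same way. Each patient is a responder or not, at one time point.

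Section 3.5 sizes the trial on this variable: "the response rate of the research subjects is the main evaluation index of observation". Its inputs are that "the response rate of the experimental group p1 is 0.56" and "the response rate of the control group p2 is 0.45", a two-sided 5% level equated with "unilateral 0.025", 90% power ("the degree of certainty that is, the 1 - *β* is 0.9"), equal allocation and a non-inferiority margin of −0.1. The result is 118 per arm, raised for 20% loss and rounded to 300 in total.

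Section 7 begins by saying that "all test data were expressed as mean and standard deviation". It then names:

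- Shapiro-Wilk and Levene checks;
- two-way repeated-measures ANOVA (group by time, with the pre-intervention visit as one level of time) with Bonferroni post hoc tests and eta-squared, if the data are normal;
- the Scheirer-Ray-Hare test with median and interquartile range, if they are not.

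It names no comparison of proportions, risk difference, confidence interval or non-inferiority test, and it does not mention the margin.

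**The concern.** The endpoint, the sample size and the analysis do not belong to the same trial. The first two describe a binary outcome judged against a margin. The third describes continuous scores tested for zero difference.

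Two things are at stake. Followed literally, Section 7 never delivers the primary result, so the analyst must choose a method for it later, possibly with the data in view. And if the response rate is put through a test of no difference, a non-significant result could be read as showing that FSN is as good as EA. That is a far weaker standard than excluding a 10-point loss.

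**Working it through.** **1. Reproduce the sample size.** Inputs from Section 3.5: p1 = 0.56 (FSN), p2 = 0.45 (EA), margin 0.10, one-sided α = 0.025, power 0.90. For non-inferiority of two proportions with unpooled variance:

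n = (1.960 + 1.282)² × [0.56×0.44 + 0.45×0.55] / (0.56 − 0.45 + 0.10)²
= 10.507 × (0.2464 + 0.2475) / 0.21²
= 10.507 × 0.4939 / 0.0441 = 117.7, rounded up to **118 per arm**, as stated.

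A two-sided 5% superiority test of 0.56 versus 0.45 with 90% power needs **433 per arm** (451 with continuity correction). The planned size is adequate only if the margin is part of the analysis.

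**2. Put the primary endpoint through Section 7 as written.**

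- A 0/1 variable is not normal, so the Shapiro-Wilk check sends it to the Scheirer-Ray-Hare branch.
- That branch reports medians. At the assumed rates the median would be 1 in the FSN arm (56% responders) and 0 in the EA arm (45%), which conveys almost nothing about the difference.
- In either branch, time includes the pre-intervention visit. Response is a change from baseline, so it is undefined there.
- Eta-squared and a rank-test p-value are not on the scale of the margin, and neither supplies a lower confidence limit.

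**3. What the sized-for analysis would give.** The standard error of the rate difference is √(0.4939/n).

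| Per arm | 95% CI half-width | Expected 95% CI around +0.11 | Power, non-inferiority at −0.10 | Power, superiority |
|---|---|---|---|---|
| 118 | 1.96 × 0.0647 = 0.127 | −0.017 to +0.237 | 90.1% | 39.3% |
| 150 | 1.96 × 0.0574 = 0.112 | −0.002 to +0.222 | 95.5% | 47.8% |

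Even at the sponsor's own assumed rates, a test of zero difference is more likely than not to be non-significant, and Section 7 gives no rule for reading that result.

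**4. Cost of reading non-significance as success.** Suppose FSN is truly at the margin: 0.35 versus 0.45.

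- At 118 per arm: z = 0.10 / √[(0.35×0.65 + 0.45×0.55)/118] = 0.10 / √(0.475/118) = 1.576. Power = P(Z > 1.960 − 1.576) = P(Z > 0.384) ≈ 0.35, so about **65%** of such trials are non-significant.
- At 150 per arm: z = 0.10 / √(0.475/150) = 1.777. Power ≈ 0.43, so about **57%** are non-significant.
- Under the margin rule (lower 95% limit above −0.10), the same truth is accepted **2.5%** of the time, by construction.

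**The case against.** The best defence is that this is a journal article. A statistical analysis plan may exist, and the interval method, covariates and analysis sets are properly left to it. The word *all* in the opening sentence of Section 7 is not strictly literal, since the section later allows medians. Its group-by-time description could be read as covering only the scored outcomes (NRS, WOMAC, 6-minute walk, SF-12). Section 3.5 already fixes the margin and the one-sided level, so the intended comparison can be inferred. Finally, nothing in the article says that a non-significant result will be read as equivalence.

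Part of this stands. The choice of interval method, covariates and a per-protocol repeat is detail the sponsor may settle elsewhere. The 57–65% range measures a risk that arises only if non-significance is misread, and the article states no such rule. The methods listed are of a suitable kind for the continuous secondary scores.

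The core does not yield. Section 7 never says that it is limited to scored outcomes, and the median branch fits a 0/1 variable no better than the mean branch. This is more than silence: the section assigns every variable to a route that does not fit the primary one, so an analysis plan that compared response rates with −0.1 would depart from the published text.

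The defence can also point out that the Abstract and Introduction speak only of comparing the two treatments, and that non-inferiority appears in Section 3.5 alone. That is a reason to state the hypothesis explicitly. It does not rescue Section 7, because non-inferiority is the only hypothesis the sample size supports.

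**Conclusion.** The concern holds and should be corrected before the data are analysed. As written, the analysis section cannot produce the primary result or judge it against the margin on which the trial was sized. The sample size itself is sound for the right analysis: about 90% power with 118 evaluable patients per arm and 95.5% if all 150 are evaluable, given the assumed rates of 0.56 and 0.45. If a non-significant difference test were used in its place, an FSN response rate truly 10 points lower would pass about 57% to 65% of the time rather than 2.5%.

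These figures use normal approximations with unpooled variance, except the superiority sample sizes and powers, which use the pooled variance under the null. The conclusion concerns the plan as published; an unseen analysis plan may already name a suitable method, in which case the two texts need to be brought into line.

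**What to change.** Add a paragraph to Section 7 that does the following:

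- States the primary hypothesis, consistent with Section 3.5: non-inferiority of FSN to EA on the week-4 response rate, margin −10 percentage points.
- Names the primary analysis: the difference in responder proportions at week 4 (FSN minus EA) in all randomised patients, with a two-sided 95% confidence interval. Non-inferiority is concluded if the lower limit exceeds −10 points; superiority may then be claimed if it exceeds 0.
- Reports response rates at every visit as n (%) with a risk difference and interval, and restricts mean and SD, ANOVA and the rank test to the continuous scores.

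Optional, and for the sponsor to choose: the interval method (for example Miettinen-Nurminen, or logistic regression standardised over centre and baseline NRS and WOMAC) and a repeat in the per-protocol set.

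The cost is one paragraph, with no new data and no change in sample size. If the sponsor in fact intends superiority, that must be said now, because the planned 150 per arm gives only about 48% power for it at the assumed rates.

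### For the continuous secondary outcomes, the baseline score is a level of the time factor and not a covariate, and groups are compared at a visit only after an interaction, so the group effect is diluted and the week-4 difference may never be estimated

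*Protocol article*

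**What the plan says.** The Statistical analysis section gives a closed list of model terms: "A total of two types of independent variables were used in this study", namely group (FSN or EA) and time. It defines the second as "the time independent variable (pre-intervention, after 1, 2, 3, and 4 weeks of intervention, and after follow-up", which makes six levels with baseline as the first. The model is named: "two-way repeated measures ANOVA (Two-Way Repeated ANOVA) was used to observe the Main Effect and Interaction of the two types of independent variables". A Bonferroni post hoc test follows "when there was an Interaction between the two". Effect size is expressed as eta-squared in three bands. If the data are not normal, the analysis switches to the Scheirer-Ray-Hare test.

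Table 2 schedules NRS, WOMAC and the 6-minute walk at T0, T1, T2, T3, T4 and T8, and SF-12 at T0, T4 and T8 only. The design section (2.1) names week 4 among the times for NRS, WOMAC and 6-minute walk. The Secondary outcomes section lists weeks 1 to 3 and four weeks after treatment.

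The primary outcome is binary: "Response rate for knee symptom relief after 4 weeks of treatment". This ANOVA does not apply to it.

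**The concern.** Baseline is measured before treatment, so in a randomised trial the expected group difference there is zero. Treating it as an outcome level has two consequences. The group main effect averages that zero with the post-treatment differences. And baseline is not used as a covariate, so the precision it could add to each later comparison is lost.

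The secondary outcomes are defined at particular visits, but the plan offers a visit-specific comparison only after an interaction. If the interaction test fails, the only between-group result left is the diluted main effect. That could happen even when there is a real and fairly constant benefit. The end-of-treatment difference in pain, function or walking, which readers will look for, would then go unestimated.

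This is not a detail left to an analysis plan. The article states the model, its terms and the condition for the post hoc test, and an unseen analysis plan would have to override them.

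**Working it through.** **The plan's own figure.** The only sample-size calculation is for the binary response rate: p1 = 0.56, p2 = 0.45, margin 0.10, one-sided 0.025, power 0.90.

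n = (1.960 + 1.282)² × (0.56×0.44 + 0.45×0.55) / (0.11 + 0.10)² = 10.51 × 0.4939 / 0.0441 ≈ 117.7, so 118 per arm.

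This reproduces the stated 118, and the present point does not alter it. The article gives no SD, effect size, correlation or power for the continuous outcomes, so the inputs below are assumptions. Arm sizes are 150 as planned and 120 (150 × 0.8, using the article's 20% loss allowance).

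**Dilution of the group main effect** (arithmetic only; Table 2 visit schedule)

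- Six times, constant effect d after baseline: (0 + 5d)/6 = 0.83d.
- SF-12, three times, constant effect: (0 + 2d)/3 = 0.67d.
- Six times, effects 0, 0.1, 0.2, 0.3, 0.4, 0.4 SD: 1.4/6 = 0.233 SD, which is 58% of the week-4 effect. The five post-baseline visits alone average 1.4/5 = 0.28 SD (70%). The rest of the drop, a factor of 5/6, is due to baseline.
- Same rise to week 4, then falling to half at follow-up: 50% of the week-4 effect.

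**Power by formula** (120 per arm, unit SD, equal correlation ρ between visits, two-sided 0.05)

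Group main effect: SE = √[(2/120)(1 + 5ρ)/6]. Week-4 ANCOVA: SE = √[(2/120)(1 − ρ²)]. Power ≈ Φ(effect/SE − 1.96).

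| Setting | Main effect: estimate, SE, power | Week-4 ANCOVA: estimate, SE, power |
|---|---|---|
| Rising to 0.4 SD, ρ = 0.5 | 0.233, 0.0986, 0.66 | 0.40, 0.112, 0.95 |
| Constant 0.3 SD, ρ = 0.5 | 0.25, 0.0986, 0.72 | 0.30, 0.112, 0.77 |
| Constant 0.3 SD, ρ = 0.3 | 0.25, 0.0833, 0.85 | 0.30, 0.123, 0.68 |

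Simulation of 2,000 trials for the first row gave 0.658 for the main effect, 0.889 for the interaction and 0.946 for ANCOVA. For the second row it gave 0.707 for the main effect and 0.607 for the interaction.

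**The gated week-4 comparison.** This was simulated with 1,500 trials per setting. The week-4 effect was 0.35 SD. Correlation was equal at 0.3, 0.5 or 0.7, or AR(1) at 0.8 per week. The effect was constant, rising then held, or rising then half waning. The gate was the interaction at p < 0.05 with Greenhouse-Geisser correction, followed by a week-4 t test. With 4 correlations, 3 profiles and 2 arm sizes there are 24 settings.

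| Per arm | Gate, then unadjusted week 4 | Gate, then Bonferroni over 6 times | Week-4 ANCOVA, no gate |
|---|---|---|---|
| 150 | 0.53–0.86 | 0.45–0.67 | 0.88–0.99 |
| 120 | 0.40–0.73 | 0.32–0.51 | 0.81–0.97 |

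The gated route was weaker than ANCOVA in all 24 settings. One setting separates the sources (ρ = 0.5, rising then held, 150 per arm): ungated t test 0.864, the same test behind the gate 0.767, gate plus Bonferroni 0.585, ANCOVA 0.939.

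**The case against.** **Unbiasedness.** Keeping baseline in the outcome vector does not bias the comparison at any single visit, and constrained longitudinal models do the same. When baseline is a time level, the interaction is the natural test of treatment. It is not diluted, and it has power 0.89 in the rising-effect example. This stands: dilution applies to the group main effect only. The gate remains, however, and eta-squared does not give a difference on the outcome's own scale.

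**Power.** A reader might infer that the ANOVA always loses power. It does not. With a constant effect and ρ = 0.3, the main-effect test beats week-4 ANCOVA (0.85 against 0.68). That test pools six visits against one and does not estimate the week-4 difference. For a like-for-like comparison, take the baseline-adjusted mean of the five post-baseline visits in the same setting: SE = √[(2/120)((1 + 4×0.3)/5 − 0.3²)] = √[(2/120)(0.35)] = 0.076, so power is about 0.97.

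**Missed visits.** A reader might infer that the plan deletes every patient with a missed visit. The article does not say so. It states "Statistical analysis was performed by SPSS26.0 software" but names no procedure and no missing-data rule. Classical repeated-measures ANOVA uses complete cases by default, and no more can be said. The sample-size allowance, "Considering 20% of lost visits as well as refusal of visits", may already cover missed visits, so it supports no retention figure.

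**Centre.** The model names no centre term, but centre adjustment is often left to an analysis plan. The remark that "patients recruited from various centers may differ in gender, age, and other disorders" leads the authors to possible subgroup analyses, not to adjustment. Its absence is not counted as an error here.

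**Conclusion.** The point holds for the continuous secondary outcomes only. On the text, baseline is a time level and not a covariate, and visit-level comparison depends on an interaction.

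The 5/6 and 2/3 dilution factors are arithmetic, given a constant effect and the Table 2 schedule. The 58% and 50% figures also need an assumed build-up, and part of that shrinkage comes from averaging early visits.

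The size of the power loss rests wholly on assumed effects and correlations. The weakness of the gated week-4 route against ungated, baseline-adjusted week 4 was consistent across the 24 settings tried. A loss for every test in the ANOVA was not shown.

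A reader might also infer that the trial's main result is underpowered by this choice. The documents do not support that: the responder outcome and its 118 per arm lie outside this model. This should be changed, but it does not threaten the primary analysis.

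**What to change.** Replace the repeated-measures ANOVA, and the normality-triggered switch to the Scheirer-Ray-Hare test, with a mixed model for repeated measures. If the switch stayed, non-normal scores would never reach the new model.

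- Outcomes: post-baseline visits only (T1–T4 and T8; T4 and T8 for SF-12).
- Fixed effects: group, visit, group-by-visit, baseline score and baseline-by-visit. Centre can be added as a fixed effect at no cost.
- Covariance: unstructured.
- Patients: all randomised patients with any post-baseline value.
- Reporting: the FSN minus EA difference with 95% confidence interval at week 4 and T8, whatever the interaction test shows, in place of the eta-squared bands.

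The cost is a rewording of the statistical section and slightly more complex model output. No added patients, visits or measurements are needed. The change should be made before any unblinded analysis, so that it is not a post hoc choice of model.
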